##### Cognitive function

Perceived cognitive function is measured using the FACT-Cog-v3, an instrument specifically developed for cancer patients [49]. It consists of 37 items organized into four sections: perceived cognitive impairments, comments from others, perceived cognitive abilities, and impact on quality of life. Each item has five response options, and the recall period covers the past 7 days.

Objective cognitive function is measured using the TMT and the COWAT. The TMT assesses domains such as attention, motor skills, processing speed, and cognitive flexibility. The instrument was validated for the Brazilian population [50]. In the first part (TMT-A), participants draw a line connecting numbers from 1 to 25 in ascending order. In the second part (TMT-B), participants connect numbers (1–13) and letters (A–L) in an interleaved numerical and alphabetical order. Participants are instructed to maintain pencil-to-paper contact during the test. A shorter completion time indicates better performance.

The COWAT assesses verbal fluency, working memory, and inhibitory control [51]. In this test, participants must say as many words as possible that start with the letters “F,” “A,” and “S” within 1 min for each letter. Proper names, repeated words, and variations in gender, number, and conjugation are not considered. A higher number of words in each test indicate better verbal fluency.

##### Pain

Pain is measured using the BPI, which has been validated for Brazilian cancer patients [52]. This instrument consists of nine multidimensional items that assess pain intensity, pain interference in the patient’s life, pain location, and treatments for pain control and relief. Responses are given on a scale from 0 to 10, reflecting the pain felt at the time of the questionnaire and in the past 24 h. Scores are calculated by averaging the total items. A higher score indicates greater pain severity.

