**Discussion:**

Our conceptual hypothesis is that both aerobic exercise programs will positively impact primary and secondary outcomes compared to the health education group alone. Additionally, due to its multi-component nature, we expect the aquatic exercise program promote more significant effects than the land exercise program on cancer-related fatigue, muscular outcomes, and pain.

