### Outcomes {12}

The primary outcome of the study is cancer-related fatigue, measured before and after 12 weeks of intervention, using the Piper Fatigue Scale (PFS). Data are presented as group means at baseline and post-intervention time points in the assessment. Cancer-related fatigue was chosen as the primary outcome because it is one of the main complaints among breast cancer survivors [11, 12].

A set of clinically relevant secondary outcomes for breast cancer survivors was established, considering the side effects of cancer and its treatment. The secondary outcomes are measured before and after 12 weeks of intervention, presented as group means at baseline and post-intervention time points in the measurements, and include:Cardiorespiratory fitness: determined by peak oxygen consumption (VO_2peak_) and ventilatory thresholds (i.e., oxygen uptake in the first ventilatory threshold—VO_2VT1_ and oxygen uptake in the second ventilatory threshold—VO_2VT2_) obtained by an incremental test on a treadmill.Muscular performance: determined by the maximum dynamic muscular strength and dynamic muscular endurance of the knee extensors.Muscle morphology: determined by muscle thickness and muscle quality of the quadriceps femoris, measured from images obtained by B-mode ultrasonography.Functional performance: determined by functional tests performed according to the procedures proposed by Rikli and Jones [40].Mental health: measured by depressive and anxiety symptoms using the Hospital Anxiety and Depression Scale (HADS).Cognitive function: determined by aspects of perceived cognitive function measured using the Functional Assessment of Cancer Therapy—Cognitive Function—Version 3 (FACT-Cog-v3) questionnaire and aspects of objective cognitive function measured by the Trail Making Test (TMT) and the Controlled Oral Word Association Test (COWAT).Pain: measured by the Brief Pain Inventory (BPI).Quality of life: measured by the Functional Assessment of Breast Cancer Therapy (FACT-B) instrument.

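### The pain score averages all Brief Pain Inventory items, including interference, location and treatment content, yet is read as pain severity

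*Protocol article*

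**What the plan says.** Under Outcomes {12}, the protocol article lists pain as a secondary outcome and names the Brief Pain Inventory as the instrument. It names no subscale.

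The Pain section, under the measurement of secondary outcomes, makes four statements in turn:

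- On content, the instrument has "nine multidimensional items that assess pain intensity, pain interference in the patient’s life, pain location, and treatments for pain control and relief".
- On response format, "Responses are given on a scale from 0 to 10, reflecting the pain felt at the time of the questionnaire and in the past 24" hours. No item is excepted.
- On the scoring rule and, directly after it, the interpretation: "Scores are calculated by averaging the total items. A higher score indicates greater pain severity".

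The Discussion paragraph of the abstract gives pain a part in the comparison of the two exercise arms. It expects the aquatic programme to show "more significant effects than the land exercise program on cancer-related fatigue, muscular outcomes, and pain".

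**The concern.** The article fixes a rule and a meaning for the score, and the two disagree. By its own account of the content, only the intensity items measure how severe the pain is. Interference is the effect of pain on daily life, which is a different construct. Where the pain is, and what is taken for it, are not degrees of severity. An average over all of these cannot be read as severity.

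Two things are at stake. First, a real change in pain intensity is spread over items that need not move with it, so the reported change can be smaller than the change in intensity. Second, the rule cannot be applied literally to all the content described. An analyst will have to decide which items to average, and several choices are defensible: all items, rated items only, intensity only or interference only. That choice should be made before the data are seen. This matters more because the case for water rests partly on pain relief: the Background and the Discussion both cite analgesic effects of immersion.

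**Working it through.** The article gives no figure for this outcome that could be reproduced. The check is a comparison of statements, followed by a short illustration of size.

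**Step 1: content against rule.** Each kind of content in the Pain section is set against the rule (average everything) and the meaning (higher is more severe).

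| Content | Can it enter a 0–10 mean? | Is it severity? |
|---|---|---|
| Intensity | Yes | Yes |
| Interference | Yes, if rated 0–10 | No, a different construct |
| Location | No natural 0–10 value | No |
| Treatment and relief | No natural value for the type of treatment | No |

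One row of four fits both the rule and the meaning.

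**Step 2: is the rule narrowed elsewhere?** Outcomes {12} names only the instrument. The Statistical methods section does not mention the score. No part of the article limits the average to certain items or separates severity from interference. The article does keep components apart for other instruments: the Piper total is built from four subscale scores, and the Hospital Anxiety and Depression Scale has separate anxiety and depression subscales.

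**Step 3: the charitable reading.** Suppose the rule means only the items rated 0 to 10. Location and treatment type then drop out, but intensity and interference are still averaged together and the result is still labelled severity.

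**Step 4: illustration of size.** Inputs:

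- Nine averaged items (Pain section), with equal weight.
- s of them are intensity items. The article gives no split, so s is an assumption and a range is shown.
- Every intensity item falls by 2 points and no other item changes (assumption).

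Change in the mean = −2s/9.

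| s | Change in nine-item mean |
|---|---|
| 1 | −2/9 = −0.22 |
| 2 | −4/9 = −0.44 |
| 3 | −6/9 = −0.67 |
| 4 | −8/9 = −0.89 |
| 6 | −12/9 = −1.33 |

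A mean of the intensity items alone would change by −2.00 in every row.

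Under the reading in step 3, with s intensity and m interference items, the change is −2s/(s + m). With equal numbers of each, it is −2/2 = −1.00.

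These are shifts in scale points, not losses of power. The standardised effect also depends on the standard deviation of each score and on the correlations between items, and the article gives neither. If interference falls along with intensity, the dilution is smaller.

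**The case against.** The best defence is that the sentence is only loosely worded. The order of the section is content, then 0–10 responses about pain felt, then averaging. A sensible reader would average the rated responses just described and leave out what cannot be averaged. On that view the gap is one of drafting, and item-level scoring belongs in the full protocol, which the article offers on request. The article gives no scoring rule at all for the breast cancer quality-of-life or perceived-cognition questionnaires.

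Part of this stands. Items that cannot be averaged would probably not be, so it would go too far to say that the score cannot be computed. But the charitable reading does not rescue the label, because interference remains in a score called severity. Nor is this a detail left to another document: the article states a rule and an interpretation, and they conflict.

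The importance should not be inflated either. Pain is one of eight secondary outcome domains. The expectation that water will beat land names pain in the abstract only. The Objectives and the Discussion state it for fatigue and physical parameters.

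A reader might also infer that a relief item runs in the opposite direction, so that more relief raises the score and cancels or reverses a true improvement. The documents do not support this. They mention "pain location, and treatments for pain control and relief" as content, which may be a single treatment domain. They do not describe a separate relief rating or give its direction. The same applies to any claim that the score could not be compared with other trials, because no other trial's scoring is shown.

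**Conclusion.** The point holds as an internal inconsistency in how a secondary outcome is scored. The average described is not the severity measure the article says it is, whether the rule is taken literally or limited to the rated items.

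The consequence is possible dilution of a change in pain intensity. Across the range s = 1 to 6, a 2-point fall on each intensity item appears as 0.22 to 1.33 points. This assumes nine equally weighted items and no change in the rest. It shows the mechanism and does not estimate the effect in this trial. The inconsistency itself needs none of these assumptions.

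The primary outcome and the sample size are unaffected. The correction is worth making before analysis, because pain is named in the abstract's water-versus-land hypothesis and the present wording leaves the choice of score open.

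**What to change.** Replace the scoring sentence in the Pain section with two definitions:

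- Pain severity is the mean of the intensity items rated 0 to 10.
- Pain interference is the mean of the interference items rated 0 to 10.

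State that location and treatment or relief items are left out of both means and reported descriptively. Name pain severity as the pain outcome for the water-versus-land comparison in the abstract, and carry the same name into Outcomes {12}.

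The cost is a wording change, recorded before the data are analysed. No new data are needed as long as the individual item responses are kept. The article supports this: responses are collected on paper forms stored for 5 years, with double data entry for secondary outcomes. It does not say whether entry is by item. If only totals were entered, the items would have to be entered from the forms.

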##### Quality of life

The Portuguese version of FACT-B is a valid and reliable tool [53] for measuring the quality of life in breast cancer patients. It is a 37-item instrument designed to measure five domains of quality of life: physical (seven items), social/family (seven items), emotional (six items), functional (seven items) well-being, as well as a breast-cancer subscale (ten items). The responses are presented on a 5-point Likert scale. Participants are instructed to select the number that best represents their response for the past 7 days. Online written permission was obtained to use this questionnaire in the study.

#### Other outcomes

Sociodemographic and clinical characteristics.

Sociodemographic, reproductive, and menstrual characteristics, along with information on family history of breast cancer, oral contraceptive use, hormone replacement therapy, smoking, and alcohol consumption, are collected through a questionnaire before the intervention. Data on tumor histological type, tumor staging, hormone receptor status, and HER-2 expression are obtained from medical records.

##### Physical activity levels

Self-reported physical activity levels are measured before and after 12 weeks of intervention using the Godin-Shephard Leisure-Time Physical Activity Questionnaire. The translated and validated Brazilian version of this questionnaire is used [54]. Participants report the number of times they perform vigorous, moderate, and light physical activities for more than 15 min per week. The weekly frequencies of vigorous, moderate, and light activities are multiplied by nine, five, and three, respectively. The total weekly leisure activity is calculated in arbitrary units by summing the products of each component, allowing for categorization of the individual as insufficiently active or active.

##### Blood pressure outcomes

Office blood pressure measurements are taken at baseline and after 12 weeks of intervention. Participants are kept in a calm environment for 5 min before a researcher measures their blood pressure using a calibrated and automated oscillometric device (Omron Healthcare Inc., Bannockburn, IL, USA). Measurements are initially performed in both arms. Then, three measurements are taken in the arm with the highest value, with a 1- to 2-min interval between each measurement. The average of these three measurements for both systolic and diastolic blood pressure is used.

##### Anthropometric assessment

Anthropometric measurements are taken before and after 12 weeks of intervention. Body mass and height are measured using a digital scale with a stadiometer (Welmy, Santa Bárbara d’Oeste—São Paulo, Brazil). Body mass index (BMI) is calculated using the equation: BMI = body mass (kg) / height^2^ (m). Waist and hip circumferences are measured with a measuring tape, with the tape placed around the navel for waist circumference and around the widest part of the hips for hip circumference. These measurements are used to calculate the waist-hip ratio.

##### Food consumption

The “Food frequency questionnaire as subsidy for programs of non-communicable chronic diseases prevention” was used to monitor changes in food consumption [55]. The instrument is administered at baseline to assess the food consumption frequency over the month prior to the start the intervention and again post-intervention to assess this information during the last month of intervention.

##### Follow-up questionnaire

Each participant completes a questionnaire post-intervention to assess their perceptions regarding safety, enjoyment, motivation, future outlook, benefits for daily life, influence of intervention partners, exercise-related fatigue, satisfaction, self-confidence in physical performance, supervision preference, changes in lifestyle including physical activity and dietary habits, and main barriers to group participation. The questionnaire consists of 14 questions about their individual perceptions of the intervention, using a 7-point Likert scale, in which “1” means “strongly disagree” and “7” means “strongly agree.”

##### Adherence assessments

Adherence is assessed by monitoring both attendance and compliance with the interventions. Attendance is tracked by recording session frequency and is expressed as the percentage of intervention sessions attended by a participant out of the total number of scheduled sessions (24 sessions for exercise programs or 12 sessions for the health education program alone). Compliance is defined as the percentage of intervention sessions performed without deviations from the protocol.

### Plans to promote participant retention and complete follow-up {18b}

To enhance participant retention and ensure complete follow-up, regular and clear communication is maintained to sustain engagement, provide appropriate incentives, and offer ongoing support to minimize dropouts. All participants are also invited to join the ERICA Project after completing post-intervention assessments. Additionally, detailed records are kept of any discontinuation or deviation from intervention protocols, including data from participants in these situations, to ensure a comprehensive and transparent analysis of study results.

### Data management {19}

At the end of each testing day, a responsible researcher verifies missing or inaccurate data and the check the backup data. Subsequently, double data entry is performed for primary, secondary, and additional outcomes. Additionally, ultrasound images of the quadriceps femoris muscles are stored and shared via a secure cloud-based platform (Google Drive).

### Confidentiality {27}

Data are collected on standardized paper forms labeled with each participant’s ID. These paper forms will be stored in LabNeuro for 5 years. After data entry into the computer, the digital data will be stored on a secure drive accessible only by the research team to maintain confidentiality throughout the trial and beyond.

### Plans for collection, laboratory evaluation, and storage of biological specimens for genetic or molecular analysis in this trial/future use {33}

Not applicable. No biological specimens will be collected in the current trial or for future use in ancillary studies.

## Statistical methods

### Statistical methods for primary and secondary outcomes {20a}

We will use descriptive statistics, including mean, standard deviation, 95% confidence intervals, and absolute or relative frequencies as applicable. The Shapiro–Wilk and Levene tests will be used to assess data normality and homogeneity. Generalized estimating equations, with Bonferroni adjustment for post hoc tests, will be used to compare time points and groups. One-way ANOVA and/or Kruskal–Wallis tests will be conducted to compare training compliance and follow-up questionnaire responses between groups. Effect sizes between groups will be calculated based on the absolute difference (± SD) between baseline and post-intervention values, using Cohen’s *d*. All statistics procedures will be performed in the SPSS vs. 28.0, with a significance level set at *α* = 0.05.

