### Trial design {8}

The WaterMama trial is a randomized clinical trial employing a 1:1:1 allocation ratio. It was designed as a superiority trial with three parallel groups, controlled by active intervention, and blinded to outcome assessors and data analysts.

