### Sample size {14}

The sample calculation was conducted using the GPower version 3.1 program, adopting a significance level of *α* = 0.05 and 90% power. Data for the calculation were derived from the study results by Kessels et al. [12] for the primary outcome of cancer-related fatigue (effect size 0.605). It resulted in a total sample size of 39 subjects. Additionally, nine individuals (approximately 20%) will be included in the study to account for potential sample losses, totaling 48 participants randomized into the three groups.

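### GEE with 13 to 16 women per arm and no stated small-sample correction: under ordinary large-sample Wald inference the true error rate exceeds 5%

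*Protocol article*

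**What the plan says.** The section on statistical methods for primary and secondary outcomes {20a} states: "Generalized estimating equations, with Bonferroni adjustment for post hoc tests, will be used to compare time points and groups". It continues: "All statistics procedures will be performed in the SPSS vs. 28.0, with a significance level set at" 0.05. It names no variance estimator for the GEE (robust or model-based), no small-sample correction and no reference distribution.

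The sample size section {14} uses an effect size of 0.605 with 90% power: "It resulted in a total sample size of 39 subjects". It then adds nine women for losses, "totaling 48 participants randomized into the three groups". The trial design section {8} describes a "randomized clinical trial employing a 1:1:1 allocation ratio". Outcomes are assessed twice, at baseline and week 13 {18a}. The section on missing data {20c} plans an intention-to-treat analysis of all randomised women with multiple imputation.

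**The concern.** In GEE the independent unit is the woman. The usual Wald inference (sandwich variance, normal or chi-square critical values) is a large-sample approximation in the number of such units. With 13 to 16 per arm, two things go wrong in the same direction. The sandwich variance of an arm's mean change divides by n where n − 1 is needed, so it is too small. The normal or chi-square reference also ignores that the variance is estimated. A Bonferroni step works further out in the tail, where the relative error is larger, so it does not bring the familywise error back to 5%.

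At stake are confidence intervals that are too narrow and a false-positive rate above the stated 0.05, for the primary fatigue outcome and for every continuous secondary outcome analysed the same way.

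**Working it through.** **Inputs.** Evaluable N = 39 and randomised N = 48 (section {14}); 1:1:1 allocation (section {8}), so 39/3 = 13 and 48/3 = 16 per arm; two time points (section {18a}); α = 0.05 (section {20a}).

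**Assumptions.** Complete data, normal change scores with equal variance in the arms, and Bonferroni over the three between-arm contrasts of change.

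**The plan's own figure.** The article does not say which test or effect-size metric gave 39. A one-way ANOVA on three groups with f = 0.605 reproduces it: λ = 39 × 0.605² = 14.27, critical F(2, 36) = 3.26, power 0.910 (N = 36 gives 0.883). A repeated-measures interaction with f = 0.3025, two time points and correlation 0.5 also gives 39. Both readings are F tests.

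**Pairwise contrast, uncorrected sandwich.** With two time points and complete data, the GEE group-by-time contrast is the difference in mean change, and the sandwich variance for each arm is SS/n². The standard error is therefore low by the factor r = √((n − 1)/n), and the true size is exactly P(|t with 2(n − 1) df| > z·r).

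| | 13 per arm | 16 per arm |
|---|---|---|
| r | 0.961 | 0.968 |
| z·r with z = 1.960 | 1.883 | 1.898 |
| df | 24 | 30 |
| Size, nominal 5% | 7.2% | 6.7% |
| z·r with z = 2.394 (α/3) | 2.300 | 2.318 |
| Size, nominal 1.67% | 3.0% | 2.7% |

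**Where the excess comes from.** With the small standard error but a t reference, the pairwise size is 5.9% and 5.7%. With an unbiased standard error but a normal reference, it is 6.2% and 5.9%. The two sources contribute about equally.

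**Familywise and 2-df tests, uncorrected sandwich.** Null simulation with 200,000 trials per sample size:
- Any of three Bonferroni contrasts significant: 7.7% at 13 per arm, about 7.0% at 16.
- 2-df group-by-time Wald chi-square: 8.8% and 8.0%.
- The same 2-df test with unbiased arm variances but still chi-square: 7.3% and 6.8%. Correcting the variance alone is not enough.

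GEE models fitted to simulated data gave 7.9% (13 per arm) and 7.5% (16 per arm) for the 2-df test in 3,000 runs each, and 8.4% in 6,000 runs with 48 randomised and nine week-13 values missing. With exponential change scores the 2-df figures were 9.3% and 8.4%.

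**Model-based variance, unbiased pooled scale.** The pairwise size is P(|t with 3(n − 1) df| > 1.960): 5.8% (36 df) and 5.6% (45 df). For the 2-df test, P(F(2, m) > 5.991/2) = (1 + 5.991/m)^(−m/2):
- m = 36: 1.1664^(−18) = 6.3%
- m = 45: 1.1331^(−22.5) = 6.0%

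Simulation gave 5.9–6.2% for this case. With the maximum-likelihood scale instead, the 2-df test runs at 7.6% and 7.1%.

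**Small-sample inference.** An F test on change, with pooled unbiased variance, gave 5.0% and 4.9%. Three Bonferroni t tests gave a familywise error of 4.4% and 4.3%.

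**The case against.** The strongest reply is that the article never says the uncorrected sandwich will be used. It names GEE, Bonferroni, the software and α, and a condensed article can leave the variance estimator to a fuller plan. A reader might infer that no correction is planned, or that the primary test will run at a flat 7–9%. The documents support neither. They are silent on the estimator, an analysis plan that is not shown could contain a correction, and an unbiased model-based variance puts the excess at about one percentage point or less for most tests. It would also be wrong to put the problem down to small standard errors alone.

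A second reply is that the planned analysis uses multiple imputation, which the figures above leave out. That stands. A separate simulation with 16 per arm, three week-13 values missing per arm, an uncorrected sandwich and Rubin's pooling with a t reference (6,000 runs per setting) gave 6.1–6.6% pairwise and 6.1–6.4% familywise. The inflation is smaller but present. The 2-df test was not examined under imputation.

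A third reply is that replacing GEE is a matter of preference. That also stands: a correction within GEE is enough.

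What remains is that the article pairs a stated large-sample method with a stated small sample, and every uncorrected Wald version examined with normal data exceeds 5%.

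**Conclusion.** The point holds in a limited form. With 13 to 16 women per arm and α = 0.05, ordinary large-sample GEE Wald inference is anti-conservative. The size of the excess depends on a choice that the article does not state:
- uncorrected sandwich: 6.7–7.2% pairwise, 7.0–7.7% familywise after Bonferroni, 8.0–8.8% for the 2-df test;
- unbiased model-based variance: 5.6–5.8% pairwise and about 6% for the 2-df test.

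These figures assume complete, normal data with equal variances and three between-arm contrasts, and they exclude multiple imputation. The causes are standard errors 3–4% too small (sandwich only) and the normal or chi-square reference. At worst, a nominal 95% pairwise interval covers 100 − 7.2 = 92.8%. That is worth correcting, but it does not undermine the trial: a cheap improvement.

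**What to change.** For the primary and continuous secondary outcomes, state the variance estimator and the reference distribution, and choose a combination valid at this size. Either of these will do:
- keep GEE, with a bias-corrected sandwich (for example Mancl-DeRouen or Kauermann-Carroll) **and** a t or F reference; or
- use ANCOVA of the week-13 value, or a REML mixed model with Kenward-Roger or Satterthwaite degrees of freedom.

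The second route would also need the imputation wording in section {20c}, which refers to GEE, to be brought into line.

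The cost is a sentence or two of text and slightly wider intervals. Against the uncorrected sandwich with a normal reference, a pairwise interval widens by 2.064/1.883 = 1.10 at 13 per arm and 2.042/1.898 = 1.08 at 16. The chosen method may need a different procedure or package from the one named ("All statistics procedures will be performed in the SPSS vs. 28.0"), which should be checked before the text is fixed. Recruitment, assessments and interventions are unaffected. The change should be made before any unblinded analysis.

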## Data collection and management

### Plans for assessment and collection of outcomes {18a}

On the initial visit, after signing the consent form, each participant completes a questionnaire covering their clinical and sociodemographic characteristics. During this visit, familiarization procedures are also performed with the knee extension equipment, treadmill, and RPE scale to mitigate potential learning biases and ensure participants’ proficiency in performing the tests before formal data collection.

The study outcomes are assessed at two time points: baseline (weeks 0) and post-intervention (week 13). All randomized participants undergo outcome assessments, irrespective of their attendance or completion status. Participants who withdraw from the study at any time after randomization are still invited to complete the final evaluations (week 13), ensuring data inclusion in the intention-to-treat analysis. Measurements are performed in two separate visits, apart at 48-h interval to avoid interference among them, according to the sequence:Visit 1: quality of life questionnaire, cancer-related fatigue questionnaire, perceived cognitive function questionnaire, mental health questionnaire, maximal dynamical strength of knee extensors, dynamic muscular endurance of knee extensors, and functional testsVisit 2: quality and thickness of quadriceps, objective cognitive function instruments, pain questionnaire, physical activity levels questionnaire, anthropometric measurements, office blood pressure, cardiorespiratory fitness test and food frequency questionnaire

Participants are instructed to avoid intense physical activity 72 h before the first evaluation session (week 0). Post-intervention evaluations take place 72 h after the last training session. In addition, the follow-up questionnaire is applied on the last visit of the final evaluations.

The same investigator applies each test at baseline and post-intervention time points to ensure consistency. Outcome assessors are trained, and standardized procedures are performed for each assessor during assessments. In addition, the same investigator applies the questionnaires individually at baseline and post-intervention time points in a reserved room.

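### No adjustment for baseline fatigue is stated for the primary analysis; the analysis is valid, but it gives up precision that a trial of 13 to 16 women per arm could have at no cost

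*Protocol article*

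**What the plan says.** - **Model** (Protocol article, Statistical methods for primary and secondary outcomes {20a}): GEE, with Bonferroni-adjusted post hoc tests, "will be used to compare time points and groups". No covariate, model term, working correlation or primary contrast is given.
- **Effect size** (same section): "Effect sizes between groups will be calculated based on the absolute difference" from baseline to post-intervention, expressed as Cohen's d. This is unadjusted change.
- **Outcome definition** (Outcomes {12}): "Data are presented as group means at baseline and post-intervention time points in the assessment".
- **Time points** (Plans for assessment and collection of outcomes {18a}): "The study outcomes are assessed at two time points: baseline (weeks 0) and post-intervention (week 13").
- **Timing of baseline**: the schedule under Participant timeline {13} puts the baseline fatigue questionnaire before allocation, and Concealment mechanism {16b} has allocation follow the baseline evaluation. Randomisation is stratified by endocrine therapy, not by fatigue (Sequence generation {16a}).
- **Sample size** (Sample size {14}): "It resulted in a total sample size of 39 subjects", raised to 48, for an effect size of 0.605 at α = "0.05 and 90% power". The section gives no SD and no correlation between baseline and post-intervention scores.

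**The concern.** Read together, these sections treat baseline PFS as one of two outcome levels and never as information to condition on. With two time points, complete data and separate baseline means by arm, the group-by-time term of such a GEE is the difference in mean change scores. If the post hoc tests compare arms at the second time point, it is the difference in raw week-13 means. Neither uses the baseline score efficiently.

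Randomisation makes the baseline means equal in expectation, but in arms this small they can differ noticeably by chance. The standard error of a pairwise baseline difference is √(2/13) = 0.39 SD at 13 per arm and √(2/16) = 0.35 SD at 16. An adjusted contrast corrects for that imbalance, while the two unadjusted contrasts over-correct or ignore it.

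Precision is what is at stake. The hypotheses include water against land as well as each exercise arm against education, so the trial depends on pairwise contrasts between arms of 13 to 16 women.

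**Working it through.** **1. The plan's own figure.** A one-way ANOVA with three groups, f = 0.605 and α = 0.05 has noncentrality N·f² = 39 × 0.605² = 14.27. Power is 0.910 at N = 39 and 0.883 at N = 36, so 39 reproduces. It also reproduces under another reading: 0.605 taken as d (f = 0.3025) in a group-by-time interaction with two measurements and an assumed r of 0.5. Noncentrality is then 0.3025² × 39 × 2/0.5 = 14.27, with power 0.910. The documents therefore do not settle what 0.605 measures, which matters in step 5.

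**2. Variance of a pairwise arm difference.** Assume the same SD at both times and correlation r between them. In units of SD², with n per arm:

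- change score (group-by-time, baseline means free): 2(1-r) × 2/n
- week 13 only: 1 × 2/n
- adjusted for baseline: (1-r²) × 2/n

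The ratio of adjusted to change is (1-r²)/[2(1-r)] = (1+r)/2. The share of attainable precision lost is therefore (1-r)/2 for change and r² for week 13 only.

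**3. Results over a range of assumed r.**

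| r (assumed) | Loss, change: (1-r)/2 | Reduction in SE: 1-√((1+r)/2) | Loss, week 13 only: r² |
|---|---|---|---|
| 0.3 | 35% | 19% | 9% |
| 0.5 | 25% | 13% | 25% |
| 0.7 | 15% | 8% | 49% |
| 0.8 | 10% | 5% | 64% |
| 0.9 | 5% | 3% | 81% |

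The two losses move in opposite directions with r, so no single range covers both contrasts.

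**4. At this trial's size.** Estimating the baseline slope costs a little. The adjusted variance is multiplied by about 1 + 1/(N-5), which is 1.029 at N = 39 and 1.023 at N = 48. The net reduction against change is then:

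- r = 0.3: 1 - 0.65 × 1.029 = 33% at N = 39 (34% at N = 48)
- r = 0.5: 1 - 0.75 × 1.029 = 23% (23%)
- r = 0.7: 1 - 0.85 × 1.029 = 13% (13%)

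Simulation at 13 and 16 per arm gave 32-34%, 20-25% and 11-13%. It also confirmed what the GEE estimates. At 16 per arm and r = 0.5, the group-by-time contrast had variance 0.122 (theory for change: 0.125). The baseline-adjusted regression gave 0.094, and the same GEE with one common baseline mean gave 0.100.

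**5. Illustrative power.** Read 0.605 as a pairwise difference in SDs, take r = 0.5 and test at 0.05/3, two-sided, with the residual SD pooled over the three arms.

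| n per arm | SE, change | SE, adjusted | Power, change | Power, adjusted |
|---|---|---|---|---|
| 13 | √(1 × 2/13) = 0.392 | √(0.75 × 2/13 × 1.029) = 0.345 | 18% | 24% |
| 16 | √(1 × 2/16) = 0.354 | √(0.75 × 2/16 × 1.023) = 0.310 | 23% | 31% |

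At 16 per arm the same calculation gives 16% to 25% at r = 0.3 and 40% to 46% at r = 0.7.

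**The case against.** **A condensed article may omit covariates.** Nothing in the methods section forbids a baseline term, and a fuller plan could name one. That stands as a caution about the model's terms. It does not remove the point: the article does fix a method, and its between-group effect size is explicitly raw change. A better method than the one stated can be named.

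**No error is shown.** This stands. A reader might infer that the planned comparison is biased, for instance because eligibility sets no minimum fatigue and regression to the mean enters the change scores. The documents do not support that. Under randomisation any regression to the mean is the same in every arm in expectation, and having no entry threshold lessens it. What remains is chance imbalance, which is the precision point already counted.

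**Treating baseline as a repeated outcome is not the fault.** This stands too. The same GEE with a common baseline mean recovers the precision. The loss comes from leaving baseline means free by arm.

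**The size is not in the documents.** It is tempting to state a flat loss of 15-35%. That range needs an assumed r of 0.7 to 0.3, a group-by-time reading and the variance scale. The protocol supplies none of these, and a high correlation would cut the loss to 5-10%.

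**The power figures are conditional.** If 0.605 is Cohen's f, the implied difference between the extreme arms is 0.605 × 3/√2 = 1.28 SD to 0.605 × 2/√(2/3) = 1.48 SD, and these pairwise powers do not apply. Even as read here, adjustment adds 6 to 8 points at r = 0.5 and does not by itself make the trial well powered.

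**Conclusion.** The concern holds as a point of efficiency, not of validity. The stated analysis names no adjustment for a baseline score that is measured before allocation, and it reports effect sizes on raw change.

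Its cost depends on two things that the protocol leaves open: the contrast and r. Read from group-by-time, the loss is (1-r)/2, which is worth having back in a trial this small when r is moderate and is minor when r is 0.8 or more. Read from week 13 alone, the loss is r² and becomes serious as r rises. The formulas assume equal SDs at the two times and complete data, and the net gain at 13 to 16 per arm is slightly below the large-sample figure. The change is recommended; without it the trial would still be interpretable.

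**What to change.** Before unblinded analysis:

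- Define the primary contrast as the between-arm difference in week-13 total PFS, adjusted for baseline PFS. Either a regression of week-13 PFS on arm with baseline PFS as covariate, or the planned GEE (or a mixed model) with one common baseline mean across arms, will do this.
- Report each adjusted difference with its confidence interval, and base the between-group effect size on that difference instead of raw change.
- Use the same form for every continuous secondary outcome, each with its own baseline.

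This also settles which comparison is primary, which the current wording does not. The cost is a change of analysis wording: baseline measurement is already in the assessment schedule, so no extra participants, visits or instruments are needed.
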